## **1 Abstract**

Undernutrition remains one of the biggest challenges in developing countries. Children aged 0-23 months are the most vulnerable group with a peak incidence of mortality and morbidity. The Cambodian Demographic and Health Survey 2010 estimated a national stunting prevalence of 40%. Results show that stunting increases after six months of age when most children receive complementary feeding. The promotion of a nutrient-dense diet based on locally available foods is essential to improve the nutritional status of young children. In order to optimize infants and young children's diets, the FAO project "Improving food security and Market Linkages for Smallholders in Otdar Meanchey and Preah Vihear Provinces (MALIS)" will implement a food security project with a nutrition education component.

The objective of the research is to evaluate the effectiveness of the behavior change messages which will be delivered through a community based intervention involving community based organizations. The research design encompasses both qualitative and quantitative methods, including two cross-sectional surveys, focus group discussions and key informant interviews. The first cross-sectional survey will take place prior to the intervention to assess the baseline nutrition security situation of families with children below two years in the MALIS project region. The behavior change communication strategies will be implemented in the prior selected intervention areas by the MALIS project. The second cross-sectional survey will be conducted after at least 18 months of intervention evaluating the impact of the intervention by a research team.

The primary outcome parameter to be measured will be mean Height for Age z-Scores (HAZ). Secondary outcome parameters will be vitamin A deficiency, iron deficiency and behavior change. Methods for data collection will include anthropometric measurements, questionnaires, collection of blood plasma by finger prick and focus group discussions. Statistical analysis will compare primarily the difference of the mean height-for-age z-score of children in intervention and control areas.

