## **6.6 Statistical methods and analysis**

Data assessment and data analysis will follow the adopted UNICEF framework of underlying causes of malnutrition and mortality (see Chapter 3.1). Nutritional status will be interpreted as a result of household food security, i.e. access to food and food availability, adequate social and care environment, i.e. direct caring behaviors, women's role, status and rights, social organizations and networks, and functioning public health system, i.e. health environment and access to health.

The cross sectional surveys will be used to gather information of the above mentioned parameters before and after the intervention. The data will be entered into the SPSS editor (IBM SPSS Statistics version 20) and checked for inconsistencies by two individuals independently. Flagged values will be checked based on the filled questionnaires and if applicable the study participants will be approached to verify the result.

Statistical analysis will be performed using the statistical packages of IBM SPSS statistics (version 20). At first the variables will be tested for normal distribution, followed by a descriptive analysis of prevalence of malnutrition, anemia, vit-A deficiency, respiratory infections and fever (ARI), diarrhea, morbidity rates, dietary diversity, and knowledge of age appropriate feeding. The latter involves a development of a score to describe the knowledge about age appropriate feeding. Further, regression analysis will be applied looking for causalities of malnutrition in the studied area.

Focus group discussions will be based on a general interview guide approach. The interview guide will include subjects of implementation, acceptance and obstacles of TIPs. They will be analyzed by applying the content analysis according to Mayring (51) and facilitated by the use of MAXQDA©-software (53).

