### **6.8.2 Anthropometric measurements**

A central weighing and measuring station will be installed in every village. After the interview, mothers/caretakers (if possible the father as well) and their children will be

send to the weighing and measuring station. Weight and height of children and adults will be measured according to an anthropometric protocol based on the WHO report “Physical status: the use and interpretation of anthropometry” (1995) (60).

Weight of children will be determined with the child wearing no clothing. Adults’ weights will be taken while wearing light indoor clothing and no shoes. Heights and weights will be assessed to the nearest 0.5 cm and 0.1 kg, respectively. To determine the nutritional status of pregnant women, mid-upper arm circumference (MUAC) will be measured. All measures will be taken twice and the mean value is used for analysis (see ISAK manual (61)).

Anthropometric measurements will be taken with standardized equipment from Seca (SecaGmbH & Co KG, Hamburg, Germany). Weight will be measured using standardized digital flatscales (Seca 874, capacity: 200 kg) with mother/child function. Infants and small children are weighed while being held by the mother. The weight of the mother is assessed separately. Then the Mother-Child function ascertains the tare of the weight. Recumbent length will be taken from children with measuring boards (Seca 417, measurement range: 10–100 cm).

The height of adults will be measured with a stadiometer (Seca 213, measuring range: 20 – 205 cm). A non-stretchable measuring tape will be used to take MUAC (Unicef). After the weight and length assessment the children will be tested for edema. Edema will be diagnosed by applying moderate finger pressure on the tops of the child’s feet. If there is edema, an impression will clearly remain for at least a few seconds (on both feet). Edema will be recorded as absent, mild (both feet/ankles), moderate (both feet/ankles plus lower legs, hands or lower arms) and severe (generalized edema including both feet, legs, hands, arms, and face) (49).

Two pairs of trained research staff, each consisting of a measurer and an assistant, will take all measurements. Privacy of the participants while taking their measurements will be assured.

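### Section 6.8.2 averages two length readings with no stated agreement limit or third reading, so half of a gross reading error can enter a child's HAZ

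*Protocol*

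**What the plan says.** Section 6.8.2 sets the rule for repeated readings: "All measures will be taken twice and the mean value is used for analysis". The sentence ends with a reference to the ISAK manual. Earlier in the section, height and weight are said to be "measured according to an anthropometric protocol based on the WHO report". Neither text is reproduced. The section gives no permitted difference between the two readings, no third reading and no rule for setting a reading aside.

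On resolution and staff: "Heights and weights will be assessed to the nearest 0.5 cm and 0.1 kg, respectively"; "Two pairs of trained research staff, each consisting of a measurer and an assistant, will take all measurements". It is not said whether both readings come from the same pair of staff.

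Section 6.6 adds a check at data entry: "Flagged values will be checked based on the filled questionnaires and if applicable the study participants will be approached to verify the result". What makes a value flagged is not stated. Section 6.9.4 provides training, visits to the measuring station and retraining.

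Mean HAZ is the primary outcome (section 1). The level of stunting is also a variable in the restricted randomization (section 6.5). Families receive a card with the anthropometric results (section 6.7.1), and its template includes the child's HAZ (annex 10.3).

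**The concern.** Two readings can show that something went wrong, but not which reading is wrong. In infants and toddlers, a bent leg or a misread digit can give an occasional error of several centimetres. A plain mean of one good and one bad reading keeps half of it.

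The later checks are poorly placed to find this. If the wrong reading is what was written down, comparing the entered value with the form confirms it. A shift of about one HAZ unit also leaves a plausible value. Visits and retraining act on staff, not on one discordant pair of readings. An analysis plan cannot repair the loss afterwards, because the information that settles the matter is a third reading taken while the child is at the board.

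At stake are added noise in the primary outcome, some wrong stunting classifications, and some wrong results on the family card.

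**Working it through.** **1. The plan's own sample size.** Inputs from section 6.4: two-sided 95% confidence, 80% power, SDs 1.5 and 1.2, a 15% change from a mean of −1.96.

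- Difference: 0.15 × 1.96 = 0.294. Variance sum: 1.5² + 1.2² = 3.69.
- n = (1.96 + 0.8416)² × 3.69 / 0.294² = 335.07, matching 335. (The printed means give 0.30 and n = 322; this is rounding of −1.666.)
- 335 × 1.54 = 515.9, matching 516 per arm after the design effect.
- Power at 516: Φ(0.294 / √(3.69 × 1.54 / 516) − 1.96) = Φ(0.84) = 80.0%.

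**2. One gross error.** With true length L and error E in one reading, the mean is (L + L + E)/2 = L + E/2. The HAZ shift is (E/2) divided by the centimetres per HAZ unit. The documents do not give that conversion; 2.0 to 3.2 cm under 24 months is assumed.

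- E = 5 cm: 2.5/3.2 = 0.78 to 2.5/2.0 = 1.25 HAZ.
- E = 10 cm: 1.56 to 2.50 HAZ.
- Effect of one such child on an arm mean of 516: at most 2.50/516 = 0.005 HAZ, against a planned 0.294.

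**3. Many errors: added variance.** Assumptions, none from the documents: a fraction f = 1% to 5% of readings is wrong by an amount uniform over 2 to 10 cm, with random sign; ordinary reading error has SD 0.3 cm; 2.4 cm per HAZ unit.

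- Mean squared gross error: (10³ − 2³)/(3 × 8) = 41.33 cm².
- Added HAZ variance with the mean of two: (0.3² + f × 41.33)/(2 × 2.4²).
- f = 1%: 0.5033/11.52 = 0.044. f = 5%: 2.1567/11.52 = 0.187.

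**4. Power.** Reading errors are independent between children, so the design effect does not multiply them: power = Φ(0.294 / √((3.69 × 1.54 + 2 × added variance)/516) − 1.96). The third-reading results come from simulating 2,000,000 children per setting, with a third reading when the two differ by more than 1.0 cm and the mean of the two closest used.

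| | f = 1% | f = 5% |
|---|---|---|
| Added variance, mean of two | 0.044 | 0.187 |
| Power, mean of two | 79.4% | 77.4% |
| Children with HAZ error above 0.5, mean of two | 1.9% | 9.1% |
| Added variance, third-reading rule | 0.009 | 0.032 |
| Power, third-reading rule | 79.9% | 79.5% |
| Children with HAZ error above 0.5, third-reading rule | 0.03% | 0.7% |
| Third reading needed, unrounded readings | 3.8% | 11.4% |
| Third reading needed, readings to 0.5 cm | 2.5% | 10% |

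Rounding to 0.5 cm hardly changes the power figures.

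**5. Sensitivity to the conversion.** Added variance scales with 1/(cm per unit)². At f = 5%, 2.0 cm gives 0.187 × (2.4/2.0)² = 0.269 and power of about 76.3%; 3.2 cm gives 0.105 and about 78.5%.

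**6. Choice of limit.** On a 0.5 cm grid, differences can only be 0, 0.5, 1.0, 1.5 cm and so on. A limit of 0.7 cm therefore means 1.0 cm or more, and calls for a third reading in about 11 to 19% of children under the same assumptions.

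**The case against.** The strongest reply is that section 6.8.2 does not stop at the mean. It points to a manual for the repeat readings and to a separate anthropometric protocol, and either may contain an agreement limit. This stands. A reader might infer that the protocol tells staff to average two readings however far apart they are. It does not say so: the text is silent on the gap and refers elsewhere. What can be said is that the protocol's own sentence is unconditional, and that any limit should appear beside it.

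A reader might also infer that the error can be corrected only at the measuring station. Section 6.6 allows participants to be approached again, and section 6.9.5 makes supervisors responsible for checking data accuracy, so an extreme value could be caught later. But no flag criterion is stated, none of these checks is tied to the difference between readings, and a moderate error can pass them.

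A third tempting inference is that the treatment comparison is biased. Errors of random sign, or errors equally common in both arms, cancel in the mean difference. Bias would need errors in one direction and in one arm only. At 5 to 10 cm in 1 to 5% of that arm's children, it would be 0.008 to 0.125 HAZ. Nothing in the documents points to such a pattern.

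The size is also open to challenge. The error rates are assumed, and trained two-person teams may do better. The planning SDs are taken from literature; if they are observed SDs they already include some measurement error, and the power loss above counts part of it twice. Working at 335 per arm gives 76.1 to 79.1%, but that multiplies independent reading error by the design effect; 516 with the design effect applied only to the planned variance is the right base.

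**Conclusion.** The point holds as an inexpensive improvement, not as an error that threatens the trial. Section 6.8.2 states neither a maximum difference nor a third-reading rule, and section 6.6 does not close the gap. The half-size carry-over is exact arithmetic; its translation into HAZ units rests on the assumed conversion.

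The consequence is noise and misclassified individual children. At the low assumed error rate the power loss is about 0.6 points; at the high rate it is about 2.6 points, of which a third-reading rule recovers most. The clearer gain is for individual results, where the share of children with a HAZ error above 0.5 falls from 1.9–9.1% to 0.03–0.7%. Whether a limit already exists in the anthropometric protocol cannot be settled from the document at hand.

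**What to change.** In section 6.8.2, replace the unconditional mean by a rule of this form: take two length readings; if they differ by more than 1.0 cm, take a third at once and use the mean of the two closest; record all readings. The 1.0 cm limit fits the 0.5 cm recording grid. Set a matching limit for weight. If the anthropometric protocol already sets limits, print those in section 6.8.2 instead.

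The cost is space on the form for a third reading, and a third length reading in about 2.5 to 11% of children under the assumptions above, by staff already at the board.

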### **6.8.3 Date of birth**

Children’s dates of birth (age) will be recorded either from immunization cards or birth registration cards. If no documents are available and the mother/caretaker doesn’t know the child’s birth-date, the age will be estimated based on the FAO Guidelines for Estimating the Month and Year of Birth of Young Children (FAO 2008) (62).

#### **6.8.4 Blood samples**

Blood samples will be taken at the central weighing and measuring station. A medical technical assistant from Cambodia will obtain the blood sample for the biochemical parameters via a finger prick using sterile disposable micro lancets to obtain capillary blood.

The analysis of biochemical measurement will include assessment of retinol binding protein (RBP), hemoglobin, transferrin receptor (TfR), acyl glycoprotein (AGP) and C-reactive protein (CRP). RBP, TfR, AGP and CRP will be analyzed using sandwich ELISA technology (63). With this technology it is possible to combine the measurements of the four proteins (TfR, RBP, CRP, AGP). Instead of using four different ELISA methods with different chemicals and procedures only one method is used. This also reduces the necessary amount of blood. A plasma volume of 2 times 7.5 µl is sufficient to do a double measurement of all four proteins. Directly after taking the blood samples they will be centrifuged and serum/plasma is stored in 0.2 mL PCR tubes. These tubes can also be directly used in an automatic pipettor to avoid the tedious and error prone manual pipetting. Samples will be stored on ice in a high efficient styrofoam box with more than 5 cm thick walls and tightly closing lid. All blood samples will be stored on ice until the end of the survey. Analysis of blood samples will be done by [name], DBS-Tech, Germany.

Hemoglobin concentration will be assessed immediately at the field site with a portable HemoCueHb301\* analyzer (HemoCue, Grossostheim-Germany) following operating guidelines (HemocueHb 301+ operating manual. HemoCue GmbH, Grossostheim, Germany).

#### **6.8.5 Motor milestones**

Motor milestones will be assessed according to the Motor Development Study component of the WHO Multicenter Growth Reference Study (MGRS) (63). The following six distinct gross motor milestones will be recorded: sitting without support, hands-and knees crawling, standing with assistance, walking with assistance, standing alone, and walking alone. To assess all milestones, the standardized testing procedures from MGRS will be adopted. A milestone will only be considered as achieved, if all given criteria are met.

### **6.8.6 Data collected Intervention**

During the intervention focus group discussions as well as open one-on-one interviews will be held with family members (especially women and elderly), health workers and nutritionists. Focus group discussions and one-on-one interviews are qualitative empirical research methods and imply that questions are posed in a colloquial manner instead of a standardized questionnaire. The focus group discussions will follow a general interview guide approach. During the focus group discussion participants are encouraged to talk freely about the subject. This will enlarge the understanding of how behavior change messages have been integrated in daily life, how behavior has changed and will as well identify obstacles to the implementation. Therefore, focus group discussions will allow gaining deeper understanding of the complex research background. (65-67).

## **6.9 Quality assurance**

### **6.9.1 Statement of Compliance**

The study will be conducted in accordance with the design and specific provisions of this Institutional Review Board (IRB) approved protocol. Good Epidemiological Practice (GEP) as recommended in the "Guidelines for proper conduct of epidemiological research" provided by the International Epidemiological Association (IEA).

The principal investigators will assure that no deviation from or changes to the protocol will take place without prior agreement from the sponsor and documented approval from the IRB. The principal investigator will promptly report to the IRB and the sponsor any changes in research activity and all unanticipated problems.

### **6.9.2 Translation of questionnaire**

Questionnaires will be designed in English and translated into Khmer by native speaking nutritionists. The translated questionnaires will be tested on three to five native speakers. To assure analogous translations, independent, native speaking nutritionists will translate both versions of the questionnaire back into English.

### **6.9.3 Recruitment of field staff**

Main requirements for enumerators are:

- language skills (Khmer)

- minimum of knowledge in nutrition related research and basic interview experiences

A total of 12 enumerators will be enrolled in the data collection process. Two medical trained research staff will be recruited from local hospitals to take blood samples and to assist the HemoCue analysis.

#### **6.9.4 Training and monitoring**

Enumerators: The enumerators will be trained on the questionnaire. A guideline on how to conduct the interview will be developed and used during the training workshop. Interviews will be conducted pairwise. One enumerator will ask the questions, the other one will record the answers. The training will as well include the correct assessment of motor milestones based on the observation criteria used in the WHO MGRS (64).

During the data collection process enumerator teams will be matched randomly every day. Interviewers will be systematically and frequently monitored and completed questionnaires will be controlled for missing data and consistency on a daily basis.

Anthropometric measurements: In order to assure that all measurements are taken in the same way the training for taking anthropometric measurements will be based on the WHO Child Growth Standards “Training Course on Child Growth Assessment” (68). Staff members of the JLU Giessen and Mahidol University will carry out the training. Furthermore the training curricula will cover issues of sensitivity to local customs, dress, and practices of modesty. Correct handling of equipment will as well be included in the training. To avoid problems in this area, observers of the same sex as the subjects will be employed. Since the research project mainly focuses on young children and their mothers/caretakers, women will be recruited to take the measurements. Survey leaders will frequently visit the weighing and measuring station. These visits will serve to verify that the anthropometry protocol is being implemented properly and consistently. Retraining sessions will be arranged when a lack of standardization is observed among the researchers.

#### **6.9.5 Assurance of communication**

Supervisors are responsible for the technical quality of the surveys for which the survey teams under their charge are conducting. Enumerators will be randomly assigned to a supervisor. One supervisor will be in charge of three survey teams.

The duties of a supervisor include advice and control of the accuracy of the survey data. The research team will include a translator for the research supervisors from Germany. This will assure the communication between all research team members as well as participants. Survey leaders and survey supervisors will record all important points in a notebook as soon as possible, including observations, ideas, problems, actions taken to address these problems, and the reasoning behind any decisions taken. Survey leaders, supervisors, and surveyors will meet daily after the survey implementation.

#### **6.9.6 Pretest**

A pretest of the entire data collection process will be conducted in villages not selected for the baseline survey. The pretest serves to ensure that the questionnaire is fully understood by the enumerators as well as to test the enumerators' behavior in conducting the interviews. The results will be evaluated by the trainers and a final consultation is held with the enumerators. Difficulties encountered by the enumerators with the questionnaire will be discussed and eventually phrasing or translations will be adjusted. The aim is to clarify any remaining uncertain points and to reach an agreement on the final questionnaire to be used.

#### **6.9.7 Registration of the study**

The IMCF research study will be registered at the German Clinical Trials Register (DRKS). The DRKS is an open access online register for clinical trials, which allows all users to search, register and share information on clinical trials. The DRKS is free and publicly accessible. The DRKS is an approved Primary Register in the WHO network since October 2008 and thus meets the requirements of the International Committee of Medical Journal Editors (ICMJE).

#### **6.10 Data protection**

Data management procedures will protect confidentiality of all data collected on individuals. All Investigators and study site staff involved with this study must comply with the requirements of the respective data protection laws in Cambodia and Germany with regard to the collection, storage, processing and disclosure of personal information. Access to collated participant data will be restricted to the survey management and stored in a locked cupboard.

Each subject will be assigned a unique identification code that will be used for data entry and analysis. To safeguard confidentiality, subject records are accessible only to the team doing the initial data entry, and the individual checking as a part of the dual entry system. Computers used to collate the data will have limited access measures via user names and passwords. Identity information and consent forms are not kept in the main computerized data file, but in a hard copy kept in a locked cabinet available only to the principle investigators. The front page of the individual record with consent and individual identity information is separated from the rest of the record, which contains only the individual code number.

Test tubes and specimens used by laboratory staff will be labeled by individual code numbers only. The collected blood samples will only be used for the specific purpose covered by the informed consent given.

Published results will not contain any personal data that could allow identification of individual participants.

